### Null hypothesis

1.1

0.8% Metronidazole gel, 0.2% Chlorhexidine gel and combination of both Metronidazole and Chlorhexidine gels are equally effective in reducing gingival inflammation.

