### Objective

2.1

To compare 0.8% Metronidazole gel, 0.2% Chlorhexidine gel and alternate application of the two gels in reducing gingival inflammation when used for 14 days as an adjuvant with home based oral hygiene instructions.

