#### Primary outcome measure

2.1.1

Bleeding index (BOP in percentage) [Two weeks and six weeks]

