### Sample size

2.5

Sample size is calculated by sample size calculator (sample size determination in health studies, WHO). Pradeep et al. [18] reported that the mean gingival index score at 6 weeks interval in Metronidazole gel group was 1.43 ± 0.27 while the mean gingival index score in Metronidazole and Chlorhexidine combination gel was 1.01 ± 0.38.

Keeping the above difference at the level of significance (α) at 5% and power of study (1-β) at 95%, we need at least 22 observations. We inflated the number to get 30 subjects per group.

Since, we have three experimental groups, so we need a total of 90 subjects.

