### Procedure

2.9

On the first visit after clinical examination, the specially designed baseline study proforma will be filled-in. The bleeding sites, probing depth and the gingival index score will be calculated for all the teeth (six sites per tooth).

Group A subjects will be instructed to apply a standard 0.2 % Chlorhexidine gel (clinica gel) on the marginal gingiva for the next 14 days, twice a day for 3 minutes, after morning and evening tooth brushing.

Group B subjects will be instructed to apply 0.8 % Metronidazole gel (anaerobic gel) twice daily for 2 minutes for two weeks.

Group C subjects will be instructed to apply 0.2% Chlorhexidine gel (clinica gel) on the marginal gingiva after morning tooth brushing and 0.8% Metronidazole gel (anaerobic gel) after evening tooth brushing. Subjects in these groups will receive the detailed and precise instruction and demonstrations on the diurnal alternate application of the two gels.

The application of the topical gels will be halted after 2 weeks and second clinical examination will be carried out for bleeding sites, probing depth and the gingival index score for all the teeth (six sites per tooth). Scaling & polishing of teeth in all three groups and oral hygiene instructions will be reinforced. Subjects will be recalled at 6 weeks for evaluation of gingival and oral hygiene indices. The reading will be recorded in the study proforma.

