## Data analysis

3

Data will be analyzed using SPSS version 20. Descriptive statistics for variables such as age, baseline clinical parameters including probing depth, bleeding sites, gingival index, and oral hygiene index will be computed. An intention to treat analysis approach will be adopted. Generalized estimation equation (GEE) will be run to account for the correlated data (six probing sites per tooth) for the comparison of study arms. Friedman test will be used to assess the bleeding sites among three study groups at the baseline and endpoint. Similarly, gingival index and oral hygiene index in the three groups at baseline, after 2 weeks and 6 weeks will be compared. The level of significance will be kept at 0.05.

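### BOP% is primary at two unranked visits under one flat 0.05, with no rule for comparing three arms; if both visits are tested, the primary error rate is about 7–10%, and higher if pairs are tested ungated

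*Protocol article*

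**What the plan says.** All references are to the protocol article.

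- **Primary outcome measure (2.1.1):** "Bleeding index (BOP in percentage) [Two weeks and six weeks". Neither visit is ranked above the other.
- **Objective (2.1):** "To compare 0.8% Metronidazole gel, 0.2% Chlorhexidine gel and alternate application of the two gels in reducing gingival inflammation".
- **Null hypothesis (1.1):** a single global statement, "0.8% Metronidazole gel, 0.2% Chlorhexidine gel and combination of both Metronidazole and Chlorhexidine gels are equally effective in reducing gingival inflammation". No pairwise hypotheses are listed.
- **Data analysis (3):** "Friedman test will be used to assess the bleeding sites among three study groups at the baseline and endpoint". The endpoint is singular and not defined. The sentence after it assigns baseline, two weeks and six weeks to the gingival and oral hygiene indices. A GEE is planned "for the comparison of study arms", without contrasts or time points. The section closes with "The level of significance will be kept at 0.05".
- **Procedure (2.9):** bleeding sites are recorded at baseline and at the two-week examination. For the later visit the text says "Subjects will be recalled at 6 weeks for evaluation of gingival and oral hygiene indices", and bleeding sites are not named.
- **Sample size (2.5):** one pair of arms, on the gingival index at six weeks, at α 5% and power 95%, and then "Since, we have three experimental groups, so we need a total of 90 subjects".

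**The concern.** A trial with two primary visits and three arms can reach a positive primary result by more than one route. A single 0.05 with no order of testing does not say which routes count. If each route is tested at 0.05, the chance that at least one is falsely positive exceeds 5%.

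The three sections also disagree about how many routes there are. The outcome list gives two visits, the analysis gives one unnamed endpoint, and the six-week visit description omits the primary measurement. As written, which visit carries the bleeding comparison could be settled after the data are seen. What is at stake is whether a reported significant difference in BOP% carries the 5% error rate that the protocol claims.

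**Working it through.** **The plan's own figure.** Inputs from Sample size: means 1.43 and 1.01 (difference 0.42), SDs 0.27 and 0.38, α 0.05, power 0.95. Sidedness is not stated. Taking a two-sided test and the larger SD as common:

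n = 2 × SD² × (z₀.₉₇₅ + z₀.₉₅)² / difference² = 2 × 0.38² × (1.960 + 1.645)² / 0.42² = 21.3, so 22 per group.

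The stated 22 reproduces. It is a calculation for one pair, one visit and a secondary outcome, so it does not fix how BOP% is tested.

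**Set-up for the error rate.** Three equal arms and no true differences. Normal arm means, two-sided tests at 0.05, and correlation ρ between the two visits. The documents give no ρ, so a range is shown. Each setting used 1,000,000 simulated trials.

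**One visit.**
- Three-arm global test (chi-square on 2 degrees of freedom, critical value 5.99): 5.0%.
- Global test first, pairs only if it is significant: 5.0%.
- Three pairs tested ungated: 12.2%.

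**Two visits, end points by hand.** At ρ = 0 the visits are independent:
- Three-arm test at each visit: 1 − 0.95² = 9.75%.
- Ungated pairs at each visit: 1 − (1 − 0.122)² = 22.9%.

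At ρ = 1 the second visit adds nothing, and the figures fall back to 5.0% and 12.2%.

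**Two visits, simulated.**

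| ρ between visits | Three-arm test at each visit, alone or gating the pairs | All three pairs ungated at each visit |
|---|---|---|
| 0 | 9.8% | 22.9% |
| 0.3 | 9.6% | 22.4% |
| 0.5 | 9.2% | 21.3% |
| 0.7 | 8.4% | 19.6% |
| 0.9 | 7.1% | 16.7% |
| 1 | 5.0% | 12.2% |

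Gating the pairs gives the same figure as the global test alone. Under the global null a pairwise claim can occur only after a false global rejection, and in this set-up a rejection always leaves at least one pair significant.

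**Claims for the alternate regimen specifically.** Of the six possible pair-by-visit tests, four involve that regimen, and only one direction of each favours it. Under the ungated scheme, the chance of a false favourable claim for it over at least one comparator at either visit is 8.9% at ρ = 0, 8.1% at ρ = 0.5 and 6.3% at ρ = 0.9.

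**Why the gated order holds 5% at one visit.** With three arms, any two pairwise equalities together imply that all three arms are equal. If all arms are equal, the global test must first reject falsely (5%). If exactly one pair is equal, only that pair can give a false claim, and it is tested at 0.05. No other configuration is possible, so the family-wise error is at most 5% without splitting α.

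**The case against.** The strongest reply is that the protocol does not describe six tests. The null hypothesis is global, the bleeding analysis is among three groups, and no contrast or post hoc procedure is named. This stands. A reader might infer from the objective and from the two-arm sample size that all three pairs are to be tested at 0.05 at both visits, giving an error of about 20%. The documents do not say so. A single gingival-index contrast used for sizing does not show that six BOP% contrasts are planned, so 17–23% is a conditional worst case.

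Nor can a claim for the alternate regimen rest on any of six tests: chlorhexidine against metronidazole says nothing about it. The relevant figure for such a claim is about 6–9%.

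A second reply is that the singular endpoint may mean one bleeding comparison after baseline, in which case a three-arm test holds 5%. That reading is possible, but the protocol does not say which visit is meant, and it lists two as primary.

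A third reply is that multiplicity detail belongs in an analysis plan that is not shown. This covers the missing post hoc procedure. It does not cover a primary outcome that the protocol itself places at two unranked visits, nor the disagreement among three of its sections.

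Finally, the figures use normal theory, whereas the plan names GEE and the Friedman test. The exact percentages would shift, but the reason for the excess over 5% would not.

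**Conclusion.** The point holds in conditional form. The protocol names no single primary time point for BOP%, its sections differ on which visits carry the bleeding comparison, and one flat 0.05 comes with no rule for comparing three arms.

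If both visits are tested, the false-positive rate for the primary outcome is about 7–10% with a three-arm test at each visit, whether or not it gates the pairs. It is about 17–23% only if all pairs are tested ungated at both visits. With one visit the corresponding figures are 5% and about 12%.

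These figures rest on two-sided tests, a normal approximation, no true differences and an assumed between-visit correlation of 0 to 0.9. On either reading, testing both visits at 0.05 exceeds 5% unless the visits are perfectly correlated. The design need not change, but the testing rule should be fixed before unblinding.

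**What to change.** 1. Name one primary time point for BOP%. Make Primary outcome measure, Procedure and Data analysis agree on it, including whether bleeding sites are recorded at six weeks.
2. At that visit, test the three arms globally at 0.05.
3. Only if that test is significant, test the three pairwise contrasts, each at 0.05.
4. Treat BOP% at the other visit as secondary, alongside gingival index, oral hygiene index and probing depth, and report these with confidence intervals.

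The cost is one paragraph and the alignment of three sections. There is no split of α and no change in sample size. The downside is small: no pairwise difference can be claimed when the global test is not significant, and no confirmatory claim can be made at the other visit.

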## Trial status

4

Recruitment of patients is started and will be completed by the end of December 2019.

## Ethical approval and consent to participate

Ethical Approval was granted from the Ethics review committee of Aga Khan University Hospital (4577-Sur-16). The CONSORT and SPIRIT guidelines for the randomized controlled trial were followed.

## Research Registration Unique Identifying Number (UIN)

Clinicaltrials.gov NCT03142607.
